#### Secondary outcomes

Secondary outcomes for this study are perceived harms of vaping measured using the Short Form Vaping Consequences Questionnaire [36], perceived harms of smoking measured with the Short Form Smoking Consequences Questionnaire [37], motivation to vape (i.e., plan to stop, decrease, continue, or increase vaping), motivation to initiate smoking, and quitting vaping self-efficacy (i.e., 5-point scale assessing confidence about quitting vaping “someday” and “in the next 6 months”). After this study had already been registered to clinicaltrials.gov, we decided to include vaping quit attempts as a secondary outcome based on the current literature [17, 20]. We will measure vaping quit attempts by asking participants whether they have made a quit attempt since their last assessment (yes/no) and to indicate the number of attempts they have made since their last assessment.

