**Methods:**

A 2-arm pilot randomized controlled trial (RCT) will be conducted by recruiting young adults ages 18–24 who reported vaping at least once per week in the past 30 days and having never smoked cigarettes at baseline. Participants will be recruited via social media ads and be randomly assigned to an intervention arm, which will be the Live Free From E-cigarettes (LIFFE) mobile-based program (*n* = 50), or a waitlist control arm (*n* = 50). The primary outcomes are biochemically verified 7-day point prevalence abstinence for nicotine vaping, vaping reduction, and smoking susceptibility. Outcomes are measured at 2-, 4-, and 8-weeks after randomization.

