#### Secondary analysis

Secondary outcomes will also be analyzed using RM-ANOVA. Specifically, treatment effects will be examined by evaluating changes in perceived harms of vaping and smoking, motivation to vape and smoke, quitting vaping self-efficacy, and vaping quit attempts. We will also evaluate whether, compared to controls, participants in the experimental group will report greater perceptions of harms of vaping and smoking, quitting vaping self-efficacy, and vaping quit attempts, and lower levels of motivation to vape and smoke at each follow-up.

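### Quit attempts asked since the last assessment record a sustained quitter as a non-attempter at weeks 4 and 8, which weakens and can reverse those comparisons

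*Protocol article*

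**What the plan says.** The Secondary outcomes section of the protocol article adds vaping quit attempts as an outcome after registration. It measures them by "asking participants whether they have made a quit attempt since their last assessment (yes/no" and by having participants "indicate the number of attempts they have made since their last assessment". Both items cover only the interval since the previous survey.

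The Abstract gives the schedule: "Outcomes are measured at 2-, 4-, and 8-weeks after randomization". The Secondary analysis section states that "Secondary outcomes will also be analyzed using RM-ANOVA". It also sets the direction of benefit, comparing arms at each follow-up on whether "participants in the experimental group will report greater perceptions of harms of vaping and smoking, quitting vaping self-efficacy, and vaping quit attempts".

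The Primary outcomes section makes seven-day abstinence from vaping, biochemically verified, a primary outcome at every follow-up. The Limitations section says the team will report whether and when effects fade over the eight weeks, to judge whether further sessions are needed.

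**The concern.** The reference period of the item and the hypothesised direction do not fit together once someone succeeds. A person who stops and stays stopped has no reason to try again. Every survey after the one that covers the quit then records a no and a zero. On this outcome that person ranks below someone who tries and relapses in every interval.

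The design makes early quitting a natural route. The intervention is one 30-minute session given shortly after randomisation, and it teaches users to choose a quit date and prepare for it. Attempts that it prompts and that succeed may well fall in the first interval and leave zeros in the later ones.

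Two readings of the results are at risk. The arm comparisons at weeks 4 and 8 are shifted against the arm with more sustained quitters. The pattern over time is also distorted: a benefit visible at week 2 that shrinks or changes sign later would look like the waning that the Limitations section intends to report, although nobody relapsed.

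**Working it through.** **Inputs.** The protocol gives the item wording, the assessment times (so intervals of 0–2, 2–4 and 4–8 weeks) and the expected direction. It gives no expected rate of quitting or of quit attempts, so there is no figure of its own to reproduce here; its power figures do not enter. The rates below are assumptions:

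- *s*, the share who quit before week 2 and stay quit: 10% to 40% in the intervention arm, 5% to 10% in the control arm.
- *a*, the share of those still vaping who try, and relapse, in a given interval: 20% to 50%.

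**Step 1: two participants who answer truthfully.**

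| Participant | Week 2 | Week 4 | Week 8 |
|---|---|---|---|
| Quits in week 1, stays quit | yes, 1 | no, 0 | no, 0 |
| Tries once and relapses in every interval | yes, 1 | yes, 1 | yes, 1 |

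**Step 2: formulas for the share recorded as attempting.**

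- Week 2: *s* + (1 − *s*)*a*
- Week 4 or 8, as worded: (1 − *s*)*a*
- Week 4 or 8, abstainers counted as attempters: *s* + (1 − *s*)*a*

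The last two differ by *s*. The item as worded therefore lowers the arm difference by exactly *s*(intervention) − *s*(control), whatever the attempt rates. With equal attempt rates the as-worded difference is −*a* times that gap, which is negative whenever the intervention arm has more sustained quitters.

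**Step 3: central example** (*s* = 20% vs 10%, *a* = 30% in both arms).

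- Week 2: 0.20 + 0.80 × 0.30 = 44% vs 0.10 + 0.90 × 0.30 = 37%, a difference of +7 points.
- Weeks 4 and 8, as worded: 0.80 × 0.30 = 24% vs 0.90 × 0.30 = 27%, a difference of −3 points.
- Weeks 4 and 8, abstainers counted: 44% vs 37%, a difference of +7 points.

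**Step 4: range.** Differences at week 4 or 8, intervention minus control, in percentage points, shown as worded / abstainers counted:

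| Sustained quit | *a* 20% both | *a* 30% both | *a* 50% both | *a* 40% vs 30% |
|---|---|---|---|---|
| 10% vs 5% | −1.0 / +4.0 | −1.5 / +3.5 | −2.5 / +2.5 | +7.5 / +12.5 |
| 20% vs 10% | −2.0 / +8.0 | −3.0 / +7.0 | −5.0 / +5.0 | +5.0 / +15.0 |
| 30% vs 10% | −4.0 / +16.0 | −6.0 / +14.0 | −10.0 / +10.0 | +1.0 / +21.0 |
| 40% vs 10% | −6.0 / +24.0 | −9.0 / +21.0 | −15.0 / +15.0 | −3.0 / +27.0 |

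With equal attempt rates the sign is always wrong as worded. With a higher attempt rate among continuing intervention vapers the contrast shrinks and reverses only in the last row. In the central example the break-even rate in the intervention arm is 0.30 × 0.90 / 0.80 = 33.8%.

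**Step 5: the cumulative outcome.** The 44% vs 37% also holds for any attempt since randomisation if the same continuing vapers try in every interval. If attempts are instead independent across intervals, the shares are:

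- Week 4: 0.20 + 0.80 × (1 − 0.7²) = 60.8% vs 0.10 + 0.90 × (1 − 0.7²) = 55.9%, a difference of +4.9 points.
- Week 8: 0.20 + 0.80 × (1 − 0.7³) = 72.6% vs 0.10 + 0.90 × (1 − 0.7³) = 69.1%, a difference of +3.4 points.

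The sign is right in both cases.

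**The case against.** **The data for the right outcome are already collected.** Consecutive intervals cover the whole period since randomisation for anyone who completes every wave, so a cumulative variable is a derivation that an analysis plan could supply. This is true and makes the fix cheap. But the article does fix the analysis: it compares quit attempts at each follow-up, in the stated direction, on an item it defines by interval. Followed as written, it gives the result above.

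**The example is built to reverse.** It assumes lasting early quits and no effect on attempts among those still vaping. A 3-point difference is 1.5 participants in 50, against a standard error of √(0.24 × 0.76/50 + 0.27 × 0.73/50) = 8.7 points. This stands as a limit on size. A reader might infer that the comparison must reverse; the last column of the table shows that it need not. What does not depend on the attempt rates is the loss, which equals the difference in sustained quitting.

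**Sustained quitters are captured elsewhere.** Abstinence is itself a primary outcome at every follow-up, so the primary results are untouched. This stands too.

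**A wider reading does not hold.** A reader might infer the same bias for motivation, described as "motivation to vape (i.e., plan to stop, decrease, continue, or increase vaping", and for self-efficacy, described as a "5-point scale assessing confidence about quitting vaping", since neither description mentions people who have already stopped. The article does not support that. It states no scoring rule for abstainers, and the full response options and any skip logic may sit in the survey instrument, which is not shown. A quitter could answer in the favourable direction: high confidence, or a plan to stop. The hypothesis names "quitting vaping self-efficacy, and vaping quit attempts, and lower levels of motivation to vape and smoke at each follow-up", so a low motivation score counts as benefit.

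**Conclusion.** The point holds for quit attempts at weeks 4 and 8. The interval item, combined with the expectation of more attempts at each follow-up, records a sustained quitter as a non-attempter after the first survey that covers the quit. The arm difference is then too low by the difference in sustained-quit shares: 10 points in the central example, turning +7 into −3. Over the assumed rates the as-worded difference is −1.0 to −15.0 points with equal attempt rates, where counting abstainers gives +2.5 to +24.0. It is +7.5 to −3.0 points if continuing intervention vapers try more often.

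Attenuation follows whenever the intervention arm has more sustained quitters; reversal is possible but not certain. The sizes rest on assumed rates, because the protocol gives none. Week 2 is unaffected for those who quit before it, and only a secondary outcome is touched. The point is still worth correcting, because the distortion resembles the fading effect that the team plans to look for.

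**What to change.** Define the outcome as any quit attempt since randomisation by weeks 2, 4 and 8, derived from the consecutive interval items. Count a participant who is abstinent at a wave as having attempted, and state which abstinence definition applies. Compare arms at each time by logistic regression, and report the number of attempts cumulatively.

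The cost is one derived variable and a sentence in the analysis section, with no new survey item or contact. There are three drawbacks:

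- A participant who misses a wave has a gap in the cumulative history unless the next report covers it. The rule for that case should be stated.
- Entry requires vaping on only one day per week, so an infrequent vaper may be abstinent for seven days without having tried to quit. A sensitivity analysis on reported attempts alone would show how much this matters.
- A cumulative share can only rise, and the arm difference may narrow as continuing vapers accumulate attempts, as in step 5. Its time trend should not be read as waning.

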#### Covariates

Because the use of other tobacco products and substances are common in young adults [38–41], we will ask participants to report whether they have used other nicotine products (e.g., oral nicotine pouches, cigars, hookah), cannabis, and alcohol at baseline and follow-up timepoints. Those who indicate current use of other nicotine products (aside from combustible cigarettes) will not be excluded, as they may benefit from engaging in vaping cessation efforts. Additionally, because it is possible that participants may have initiated cigarette smoking during their participation in the study, we will also assess for cigarette use during our follow-up assessments.

#### Intervention engagement

To ensure that participants in the intervention arm complete the intervention, we will collect backend data, which will include the percentage of completed content and the number of minutes spent completing the intervention for each participant. These were the same data collected during our initial beta test, with a 100% completion rate among the beta testers in an average of 24.29 min.

### Data analysis plan

#### Primary analysis

Treatment effects of the intervention will be examined using within-subjects repeated measures analysis of variance (RM-ANOVA), which allows for investigations of changes in mean scores over 3 or more time points. Specifically, we will evaluate two models to examine whether there were changes in past 7-day vaping frequency and smoking susceptibility across 3 time points (2-, 4-, and 8-weeks post-randomization) among those who completed the intervention. Logistic regression will be used to examine point prevalence abstinence at our 3 follow-up timepoints. Next, RM-ANOVA will be used to determine whether any changes in past 7-day vaping frequency and smoking susceptibility are the result of the interaction between the condition and time. Past 7-day point prevalence abstinence will be compared between the treatment and control groups using logistic regression. To handle missing data, we will conduct an intent-to-treat (ITT) analysis in which those who were lost to follow-up will be marked as treatment failures.

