## Objectives

In a pilot randomized controlled trial (RCT), the present study will test a brief, mobile-accessible intervention primarily built upon PNF to target vaping and the transition to smoking combustible cigarettes among young adults. The primary aim is to determine the efficacy of the program on reducing past 7-day vaping frequency and susceptibility to smoking and increasing biochemically verified 7-day point prevalence abstinence in the immediate term (2-weeks post-randomization) and short-term (4- and 8-weeks post-randomization).

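### The first primary analysis labels an uncontrolled within-arm change among intervention completers a treatment effect, and no hierarchy says that efficacy rests on the between-arm tests

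*Protocol article*

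**What the plan says.** The Objectives section sets an efficacy aim: "The primary aim is to determine the efficacy of the program on reducing past 7-day vaping frequency and susceptibility to smoking", together with an increase in verified abstinence. Trial design gives 50 participants per arm, intervention against waitlist.

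The Primary analysis section then runs in this order:

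1. It opens with "Treatment effects of the intervention will be examined using within-subjects repeated measures analysis of variance (RM-ANOVA". The models for vaping frequency and smoking susceptibility are fitted "across 3 time points (2-, 4-, and 8-weeks post-randomization) among those who completed the intervention".
2. For abstinence: "Logistic regression will be used to examine point prevalence abstinence at our 3 follow-up timepoints". This sentence names no analysis set.
3. The control arm then enters for the two continuous outcomes: "Next, RM-ANOVA will be used to determine whether any changes in past 7-day vaping frequency and smoking susceptibility are the result of the interaction" of condition and time.
4. For abstinence between arms: "Past 7-day point prevalence abstinence will be compared between the treatment and control groups using logistic regression".
5. For missing data: "we will conduct an intent-to-treat (ITT) analysis in which those who were lost to follow-up will be marked as treatment failures".

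All of these stand under the one heading, with no ranking among them. The Secondary analysis section has the same shape: treatment effects are first assessed through change, and the comparison with controls is a further step.

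Two other sections fix the analysis set in step 1. Control group gives the waitlist arm optional access only after the week 8 assessment. Study procedure says that completion is recorded from backend data once participants have been randomised and given access.

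**The concern.** Everyone who completes the programme within the 8-week window is in the intervention arm, so the analysis in step 1 is single-arm by construction. A change from week 2 to week 8 in one arm contains the intervention effect plus anything that would have happened anyway, such as natural change in vaping or the effect of answering the same survey repeatedly. The waitlist arm exists to remove that second part, and step 1 does not use it.

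The set is also restricted by a variable observed after randomisation. People who finish may differ from those who do not, although the effect may be small if nearly everyone finishes.

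What is at stake is the label and the missing hierarchy. The term treatment effects is attached to the uncontrolled test, and the section does not say which result decides efficacy. If the intervention arm changed, controls changed equally and the interaction was null, the text as written would still allow the first result to be presented as a primary treatment effect.

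**Working it through.** **The plan's own figure.** The Power analysis section gives required totals of 62, 24 and 10 for f = 0.15, 0.25 and 0.45 at power 0.8 and alpha 0.05. For RM-ANOVA with N participants, k groups, m measurements and correlation ρ, under sphericity:

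- λ = f² × N × m / (1 − ρ)
- df1 = m − 1 for time, or (k − 1)(m − 1) for the interaction
- df2 = (N − k)(m − 1)

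With k = 2, m = 4 and ρ = 0.5 (ρ is assumed, as the article states none), both the time test and the interaction test give exactly 62 / 24 / 10. With m = 3 and ρ = 0.5 they give 74 / 28 / 10. The stated figures therefore fit four measurements, which suggests that baseline was counted, while the analysis text names only the three follow-ups. The point below does not depend on this.

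**Error rate of the within-arm test when the intervention does nothing.** Inputs:

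- n = 50, the whole intervention arm (Trial design). This supposes that all complete and are followed, so the result contains no selection effect.
- m = 3, weeks 2, 4 and 8 (Primary analysis).
- Alpha 0.05 (Power analysis).
- Assumed: a linear drift of d SD from week 2 to week 8, equal in both arms, and correlation ρ.

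The three means are 0, −d/2 and −d, so f² = their variance = d²/6. Then λ = f² × 50 × 3 / (1 − ρ), on 2 and 98 df (critical F = 3.089). For d = 0.3: f² = 0.09/6 = 0.015, and at ρ = 0.5 λ = 0.015 × 150 / 0.5 = 4.5, which gives a rejection rate of 0.448.

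| Shared drift d (SD) | f² | λ at ρ = 0.5 | Rejection, ρ = 0.3 | Rejection, ρ = 0.5 | Rejection, ρ = 0.7 |
|---|---|---|---|---|---|
| 0 | 0 | 0 | 5% | 5% | 5% |
| 0.2 | 0.0067 | 2.0 | 17% | 22% | 34% |
| 0.3 | 0.0150 | 4.5 | 33% | 45% | 67% |
| 0.5 | 0.0417 | 12.5 | 75% | 89% | 99% |

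**Simulation check** (4,000 trials per row, 50 per arm, ρ = 0.5, same drift in both arms, no treatment effect):

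| Shared drift d (SD) | Within-arm time test | Condition-by-time test |
|---|---|---|
| 0 | 5.1% | 5.3% |
| 0.2 | 23.5% | 5.5% |
| 0.3 | 44.1% | 5.0% |
| 0.5 | 88.5% | 5.4% |

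The simulated within-arm rates agree with the formula to within about 1.5 percentage points. The controlled test is unaffected by shared drift.

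**Why baseline matters to the remedy.** Suppose the intervention effect is fully present at week 2 and then constant. With only weeks 2, 4 and 8 in the model there is no change over time for either test to find, and in simulation the interaction test rejects in about 5% of trials at effects of 0.3, 0.5 and 0.8 SD. With baseline added as a fourth time point it rejects in 30%, 73% and 99%.

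**The case against.** The strongest reply is that the controlled analysis is already there. The same paragraph asks whether any change is explained by condition and time, and compares abstinence between arms. Read generously, it describes change first and attributes it second, and the second step would expose a drift shared by both arms. That stands. A reader might infer that the trial lacks a controlled primary analysis, and the text does not support this. What remains is that the label sits on the uncontrolled step and that no ranking is given.

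Other stronger readings also fail:

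- **Contradiction with intention to treat.** The ITT sentence is about participants lost to follow-up, not about those who leave the programme unfinished. A completer analysis and an ITT analysis can coexist. The text does not say which models the ITT rule governs, which is an ambiguity and not a demonstrated conflict.
- **Uncontrolled abstinence analysis.** The first logistic regression sentence mentions neither completers nor a single arm. Reading it that way rests only on its position in the paragraph.
- **Regression to the mean.** Selection on recent vaping would act mostly between baseline and week 2, outside the contrast that the text describes.
- **Large selection bias.** Study procedure expects most or all to complete, after all 20 beta testers did so. That may not carry over to the trial, but nothing in the article supports a large effect. Full completion would still leave the test without a control group.

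That this is a pilot does not dispose of the point, because the stated primary aim is efficacy.

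**Conclusion.** The concern holds as one of labelling and hierarchy. The first analysis under Primary analysis is an uncontrolled, completers-only test called a treatment effect, under an efficacy aim, and nothing says that the between-arm result takes precedence over it.

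The size depends on a drift that the article does not give. At n = 50 and ρ = 0.5, the chance of a significant within-arm result with no treatment effect runs from 5% with no shared drift to 89% at 0.5 SD. The 45% at 0.3 SD is one illustrative value in that range and not a forecast. These figures assume sphericity, a linear drift that is equal in the two arms, and complete follow-up. They measure the missing control only; the effect of selecting completers is not quantified.

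**What to change.** In the Primary analysis section:

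1. State that efficacy rests only on the between-arm comparison in all randomised participants.
2. Include baseline in that model, as a time point or a covariate, so that an effect already present at week 2 is not missed.
3. Report means by week for both arms descriptively, with no within-arm test labelled a treatment effect.
4. Label any analysis of completers as secondary.

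The Secondary analysis section should follow the same order. The cost is wording in the analysis plan, settled before outcomes are analysed. Baseline is already collected, so data collection, sample size and participant procedures do not change. The downside is one fewer headline analysis.

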#### Baseline variables

The baseline survey will include an assessment of our primary and secondary outcomes (described further under Primary and Secondary Outcomes), which include e-cigarette use (e.g., past month use, days of use within the past 7 days), smoking susceptibility, perceptions of vaping- and smoking-related norms, and perceptions of vaping- and smoking-related harms. Further, we will assess for past year vaping quit attempts, motivation to quit vaping, quitting vaping self-efficacy, e-cigarette dependence, and the use of vaping harm reduction strategies. E-cigarette dependence will be measured with the E-cigarette Dependence Scale [33] and the use of vaping harm reduction strategies will be measured with the Vaping Protective Behavioral Strategies Scale [34].

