#### Primary outcomes

Our primary outcomes are reductions in past 7-day self-reported vaping frequency (i.e., the number of days they vaped, the number of times per day they picked up their device to vape, and the number of puffs taken before putting their device away per day in the past 7 days), biochemically verified 7-day point prevalence abstinence, and smoking susceptibility using the 4-item Expanded Susceptibility to Smoking Index [35]. At each follow-up assessment, participants who report 7-day abstinence will be mailed a saliva cotinine test kit to provide biochemical verification of their abstinence. Participants will be provided with written instruction on how to perform the saliva cotinine test but will also be contacted by a research team member via a Zoom video call during verification to ensure that participants are able to correctly complete the test. Results will be provided immediately via the test strip and shown to the research team member to verify. Those with a cotinine level of < 30 ng/ml will be reported as having achieved biochemically verified nicotine vaping abstinence. Participants who complete this cotinine test will be compensated with a $20 Amazon gift card.

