## Conclusions

The public health, scientific, and clinical communities have voiced the importance of curbing vaping rates among young people and increasing resources that support them with cessation. Delivering an intervention that is mobile-accessible, engaging, informative, and brief may be an innovative way to engage young adults in cessation, or at the very least harm reduction, efforts. This pilot study is the first-ever one-session vaping intervention that also aims to reduce susceptibility to smoke in young adults who vape. It aims to rigorously evaluate the effectiveness of a theory-based, empirically informed intervention, with results having potentially strong implications in the development of current and future approaches that address vaping and smoking behaviors among young adults.

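### As written, the condition-by-time test for the two continuous primary outcomes has no baseline level, so it cannot detect an effect that is present by week 2 and then stays constant

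*Protocol article*

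**What the plan says.** All references are to the Protocol article.

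- **Primary analysis, first models.** Repeated measures ANOVA (RM-ANOVA) will examine "changes in past 7-day vaping frequency and smoking susceptibility across 3 time points (2-, 4-, and 8-weeks post-randomization"). These models are run "among those who completed the intervention", so they are within-arm.
- **Primary analysis, between-arm test.** RM-ANOVA is then used to determine "whether any changes in past 7-day vaping frequency and smoking susceptibility are the result of the interaction between the condition and time". This sentence lists no time points of its own. It refers back to the changes examined in the first models.
- **Primary analysis, abstinence.** The arms are compared by logistic regression.
- **Baseline variables.** "The baseline survey will include an assessment of our primary and secondary outcomes".
- **Primary outcomes.** "Our primary outcomes are reductions in past 7-day self-reported vaping frequency".
- **Objectives.** Efficacy is to be determined "in the immediate term (2-weeks post-randomization) and short-term (4- and 8-weeks post-randomization").
- **Conclusions.** "This pilot study is the first-ever one-session vaping intervention". Under Study procedure, the session is offered after the baseline survey, with a reminder if it is not finished within 24 hours.

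Baseline is not mentioned anywhere in the data analysis plan. No main effect of condition and no contrast at a given week is named for the two continuous primary outcomes. Comparison with controls at each follow-up is planned under Secondary analysis, for secondary outcomes only.

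**The concern.** The programme is a single session offered soon after baseline, so at least part of any effect may be present by week 2, the first modelled occasion. A condition-by-time interaction over weeks 2, 4 and 8 asks whether the arm difference changes among those weeks. It does not ask whether there is a difference.

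The aim is efficacy at 2, 4 and 8 weeks, and the outcome is a reduction, which needs a pre-treatment reference. Without baseline, the named test answers neither. At stake is the between-arm conclusion for two of the three primary outcomes. A steady benefit would be missed at any size, and a significant interaction would not by itself show benefit.

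**Working it through.** **1. Inputs.** From the documents: 50 per arm, alpha 0.05, target power 0.80, Cohen f of 0.15, 0.25 and 0.45, and stated required total N of 62, 24 and 10. Assumed: no dropout, compound symmetry, correlation rho of 0.5 (range 0.3 to 0.7), and arm differences d in SD units. The article gives neither rho nor the number of measurements m used for its power figures.

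**2. The plan's own figures.** For the interaction with two arms, lambda = f² × N × m / (1 − rho), with df m − 1 and (N − 2)(m − 1).

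- f = 0.15, N = 62, m = 4, rho = 0.5: lambda = 0.0225 × 62 × 4 / 0.5 = 11.16, df 3 and 180, power 0.80.
- f = 0.15, N = 62, m = 3, rho = 0.5: lambda = 0.0225 × 62 × 3 / 0.5 = 8.37, df 2 and 120, power 0.73.

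Smallest N for 80% power:

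| Measurements, rho | f = 0.15 | f = 0.25 | f = 0.45 |
|---|---|---|---|
| Stated | 62 | 24 | 10 |
| m = 4, rho 0.5 | 62 | 24 | 10 |
| m = 3, rho 0.5 | 74 | 28 | 10 |
| m = 3, rho 0.6 | 60 | 24 | 10 |

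Four occasions at rho 0.5 match exactly. Three occasions at rho 0.6 come close.

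**3. Power of the interaction over weeks 2, 4 and 8.** With arm differences d₂, d₄ and d₈, lambda = (50/2) × Σ(d_t − mean d)² / (1 − rho), df 2 and 196. If the three differences are equal, every deviation is zero, so lambda = 0 and power = alpha = 0.05 for any d and any rho. Simulation (4,000 trials per setting; d of 0.3, 0.5 and 0.8; rho of 0.3, 0.5 and 0.7) gave rejection rates of 0.047 to 0.052.

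For a fading pattern of 0.5, 0.3, 0.1 SD at rho 0.5, the squared deviations sum to 0.04 + 0 + 0.04 = 0.08. Then lambda = 25 × 0.08 / 0.5 = 4.0 and power is 41%. The growing pattern 0.1, 0.3, 0.5 has the same deviations and the same 41%.

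**4. Baseline added as a time level.** The differences become 0, d, d, d, and the squared deviations sum to (9/16 + 3/16)d² = 0.75d². At d = 0.5 and rho 0.5, lambda = 25 × 0.75 × 0.25 / 0.5 = 9.375, df 3 and 294, power 72%.

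**5. Baseline-adjusted comparison of the mean follow-up score.** The residual variance is (1 + 2rho)/3 − rho². At rho 0.5 this is 0.667 − 0.25 = 0.417. At d = 0.5, lambda = 25 × 0.25 / 0.417 = 15.0, df 1 and 97, power 97%.

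Sustained 0.5 SD difference, by correlation:

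| Test | rho 0.3 | rho 0.5 | rho 0.7 |
|---|---|---|---|
| Interaction, weeks 2, 4, 8 (as written) | 5% | 5% | 5% |
| Interaction with baseline as a level | 56% | 72% | 92% |
| Baseline-adjusted mean follow-up | 96% | 97% | 99% |

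For a sustained 0.3 SD at rho 0.5, the three tests have 5%, 30% and 63%. For the fading pattern in step 3, the baseline-adjusted comparison has 63%, against 41% as written.

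**The case against.** **The three time points are listed for a different analysis.** They stand in the sentence on the completer models, and the interaction sentence does not repeat them. This is fair, and the reading is therefore an inference. But the second sentence follows directly, uses the same method and outcomes, and refers back to the same changes. Nothing in the analysis plan adds baseline.

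**Baseline was probably intended.** The outcomes are measured at baseline and framed as reductions, and the stated N matches four occasions. This supports the possibility without settling it, since three occasions at rho 0.6 give nearly the same N. If baseline was meant, the Primary analysis text misdescribes its own model and still has to be corrected.

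**This belongs in the full plan.** An article may leave model detail to it. Here, however, the article names both the occasions and the test.

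**RM-ANOVA also yields a condition main effect.** On the three follow-ups it would have about 86% power at 0.5 SD and rho 0.5. That softens the consequence, but the plan does not name it as the test, and turning to it after seeing the data would be post hoc.

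Two stronger inferences are tempting and not supported:

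- *An effective programme would be reported as having no effect.* Abstinence is compared between arms by logistic regression and is untouched. The main effect might be shown, and an effect that changes over time could still be detected.
- *A significant interaction would mostly mean fading.* The programme teaches users to choose a quit date and aims to move them towards considering change, so a growing effect is plausible. It triggers the test just as readily (41% in either direction in the example).

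**Conclusion.** The point holds for past 7-day vaping frequency and smoking susceptibility, on the natural reading of the Primary analysis section. The named between-arm test has power equal to alpha for any constant difference over weeks 2 to 8. That result is algebra and depends on no assumed effect size or correlation. A significant interaction would show a change in the arm difference, in either direction, and not efficacy at the stated weeks.

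The gains from including baseline do rest on the assumed 0.5 SD, compound symmetry, rho of 0.3 to 0.7, 50 per arm and no dropout. Whether baseline was intended cannot be settled from the article. On either reading, the primary and power analysis sections need to be reconciled.

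**What to change.** - **Minimum.** State that baseline is a level of time in the condition-by-time model.
- **Better.** Make the primary test for each of the two outcomes a comparison of arms adjusted for the outcome's baseline value and for sex, the stratification factor. Make it at one named week or averaged over the three follow-ups. Report arm differences with 95% confidence intervals at 2, 4 and 8 weeks.
- **Keep** condition by time over the follow-ups only for the question raised under Limitations, whether and when effects fade.
- **Reconcile** the power analysis by stating the test, the number of measurements and the correlation behind 62, 24 and 10.

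The cost is analysis-plan wording. Every score needed is already scheduled for collection.
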